### Analysis

This high-level, statistical-analysis description is meant to give an overview of what will be included in the analysis of the data collected during this trial. A more detailed description of the methodology will be provided in the Statistical Analysis Plan (SAP) [30] which will be written once this protocol has been submitted for publication. The main reasons for this are that the protocol has space restrictions of the details needed to properly describe the steps in really doing a statistical analysis, and because many research studies do not report their primary outcome findings [31] as investigators like to tell good stories from their research after spending say 5 years in doing the study, and *not* reporting on the outcomes that were in the research justification at the time of funding. The hope is that the detailed SAP will give reasons for deviating from the planned analyses to justify the changes between the funded study and the reported study, so readers can take these reasons into account when interpreting the findings from the study. More and more studies are publishing SAPs in advance of conducting the analysis of their data to follow the reasoning process and justifications if there are deviations from the initial analysis plan, and journals are linking the SAP to the protocol and results when searchers are looking for the history of the results papers.

Once the planned data are collected from the participants in the study, the data will be entered into a secure database using codes outlined in a code book, which is being developed, and will guide those making judgements about any coding details including the meaning of the numbers as well as values to display data that are missing for any reason. This will become valuable to those doing the final analysis as they get to understand these codes and take them into account during any database cleaning and statistical analysis. Once entered, and the data will be managed by looking at various descriptive statistics such as sample size, minimum, median, maximum, lower and upper quartiles, mean, standard deviation and interquartile range. Printouts of the raw data and these descriptive statistics will be scanned for anomalies and outliers by comparing the raw data to what is known about the measures. In addition, graphs including plots of distributions of each variable, boxplots and residual plots from models fitted to these data to look for influential data and possible outliers will be created. Any identified unusual data will be checked back through the data collection process to try to see if it should be considered as missing value. These reasons will be documented.

As the randomization has already been implemented, we will practice randomization integrity, taking the plan as it was derived and comparing it to the plan as it was administered in the field to see how it compares. If the randomization is implemented as designed, this will be mentioned as part of the study reports. If there are deviations, these may make the study that is planned as an RCT move more towards that of an observational study, and various analyses will have to be considered for how this should be dealt with and reported as described in the SAP. The primary analysis of the outcome variables will be using intention-to-treat (ITT) as the main method, with others as secondary analyses. Secondary analyses could include randomization as implemented or per protocol, and patterns deemed useful by the investigators. The procedure details will be included in the SAP.

There are three outcome variables being collected from each client in the study: SRQ-20, WHODAS 2.0 and CAGE. The SRQ-20 can be used as individual scores as well as primary of reporting the clients with scores either >7 or <8 to compute a rate for non-case as a proportion, and can be used as the entire interval of scores that are ordinal and so allow for ordinal statistics to be described as well as modeled. The WHODAS 2.0 and CAGE will be analyzed in the form they are scored, with no collapsing to subcategories unless later modeling justifies this. The SAP will describe what might be done in various circumstances.

Since the design of this study is a clustered stepped-wedge design, the descriptive statistics will be displayed in the order of the commune implementation in the wedging: first or second; 3-month intervals over the study; time of observation: baseline, month 1 and month 2, and combining the commune data to up to the district, combining districts up to provinces and finally combining the provinces to the entire country of Vietnam (see Fig. 2). These descriptive statistics will include those listed above: sample size, minimum, median, maximum, lower and upper quartiles, mean, standard deviation and interquartile range, with plots (raw distributions as well as box plots) of the variables by what will be considered as factors: commune, district, province, country, order of implementation and timing of the measurements within each commune. Patterns will be noted to be justified with the statistical analyses conducted later. One type of pattern from the descriptive statistics is to do LOESS smoothing to suggest patterns versus time and the timing may suggest some relationships with time, such as skill of staff within commune or order during the entire trial, that need to be considered in the modeling, as these could impact the assumptions of the stepped-wedge analysis.

Overall, the primary analysis will consider the proportions of non-caseness with the SRQ-20 within commune as the response variable using logistic regression assuming a binomial response distribution as part of the glm (generalized linear model) command in R [32]. The independent variables will be the cluster (commune), order of administration, and baseline value of the response variable, and then timing of the response at months 1 and 2. If the assumptions of the binomial data are not met, then a Poisson or negative-binomial model will be considered next, as they are known to model data better than the binomial. Standard assumptions, such as residual plotting, distributions of the residuals, influence and variance inflation, are checked to see how the models are impacted with the observations for possible deletion and remodeling. Differences between the models will be detected using AIC (Akaike Information Criterion), with smaller values detecting the better models. If some models are very close to each other, these will also be reported. Models that include higher levels of the combined communes as districts, provinces and the entire country will also be explored to gain further insight as the meaning the results. Finally, the raw scores from the SRQ-20 within commune will also be modeled, but differences between this model and the proportions model will defer to the proportions model as it was prespecified as the primary outcome variable in this protocol. In the design, we did not have a study-specific measure of the IC (intraclass correlation), we will estimate it for the four ways of doing the analysis so that future studies can use these estimates in their planning. Results will reported with *p* values in comparison with an alpha value of 0.05, and no correction for multiplicity. In addition, 95% CIs (confidence intervals) will be displayed for the results to make it easier for readers to decide whether the results are clinically important as well as their statistical significance with *p* values. Similar models and methodology will be used with WHODAS 2.0 and CAGE outcome variables. Reports will include all these analyses and any deviations will follow the SAP process for reporting. It is also possible to report all proportions as percentages for a suitable audience to understand.

At the end of the study, we may have some missing data on key variables during the study, even though we have attempted to implement the 18 methods in [33] to minimize missingness in this RCT. If the missingness is overall less than 3%, it will likely not have an impact on the interpretation of our findings [34]. However, with larger than a 3% rate, we will look at various methods for determining the kind of missingness and determine whether the analyses based predominantly on multiple imputation will impact our conclusions, using van Buuren [35] as the main guide and the R package mice (multiple imputation with chained equations) written by the same team as the book [35] which may include sensitivity analyses if these are deemed useful.

The further level of detail will be shown in the SAP to be published later than this protocol and will be be driven by some manuscripts that already have shown how it was done, as well as the various reporting guidelines in EQUATOR for cluster RCTs.

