### Design

The study uses a cluster-randomized, stepped-wedge controlled trial design. Randomization will occur at the commune level and communes will be assigned to receive either the SSM intervention first or the control condition first. The control condition will be enhanced treatment as usual. Those communes assigned to receive the control condition first will receive the SSM intervention 4 months later. This will ensure that the study is conducted ethically and will not deny evidence-based services to members of the control group. Participants in the intervention and control groups will be from different communes, or municipal districts, meaning that they do not access the same service units. This will minimize the risk of contamination. Figure 2 shows how the design will operate. The *black rows* depict the experimental data collection periods, *diagonally striped rows* are the control data collection periods, and the *gray rows* represent the long-term data collection period. The primary measure of interest is the proportion of individuals in the experimental versus the control group (*black* versus *diagonal striped*) that went from being a case of depression (SRQ-20 > 7) to being non-case (SRQ-20 < 8) over the experimental data collection period. Based on the feasibility case rate of a mean of one case every 14 days, each commune is expected to have eight completed cases (baseline, month-1 and month-2 measures) per year for a total *n* of 256 cases. Figure 3 shows a SPIRIT figure depicting the study design. Additional file 1 provides an overview of the elements of the study protocol, as described in a SPIRIT checklist.  Recruitment will continue until the desired sample size is reached and data can be analyzed to assess the effectiveness of the intervention.

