### Randomization

Randomization will be done using permuted blocks (to conceal allocation) and will be stratified by district. The randomization sequence will be developed and controlled by an individual ([name] at Simon Fraser University) not otherwise involved in the study to ensure fidelity. Details of the randomization, such as block sizes and software implementation, will be outlined in the Statistical Analysis Plan (SAP) to prevent anticipated allocation of the communes to getting the early or later timing of the SSM intervention. The SAP will be developed after this protocol is submitted for publication; however, the plan is to link them when they are published.

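### The primary glm lists no SSM/control term, and order of administration is aliased with the fixed commune effects, so the model as written cannot estimate the primary contrast

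*Protocol article*

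**What the plan says.** The Design section defines the primary measure as the share of participants moving from case to non-case on the SRQ-20, compared between the experimental and control conditions. Allocation is by commune: "Randomization will occur at the commune level and communes will be assigned to receive either the SSM intervention first or the control condition first". The design then crosses one way: "Those communes assigned to receive the control condition first will receive the SSM intervention 4 months later". Under Randomization, "Randomization will be done using permuted blocks (to conceal allocation) and will be stratified by district".

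The Analysis section takes the "proportions of non-caseness with the SRQ-20 within commune as the response variable using logistic regression assuming a binomial response distribution", fitted "as part of the glm (generalized linear model) command in R". Its terms are these: "The independent variables will be the cluster (commune), order of administration, and baseline value of the response variable". One more term follows, the visit (month 1 or month 2) at which the outcome was measured. Earlier in the same section, order is described as the commune's place in the wedge, either first or second. Study time appears there in descriptive displays and LOESS smoothing, with a remark that time patterns may need to be considered in the modelling. Models at district level and above are to be explored.

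**The concern.** A primary model has to contain a coefficient, or a contrast of coefficients, that answers the primary question. Here the question is SSM versus control, and no listed term codes it. The natural stand-in is order, but order is a property of the commune and commune is in the same model.

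The main result of the trial is at stake. An analyst who follows the text gets a fitted model with no treatment effect in it. An analyst who departs from the text chooses the primary model during or after data collection, and the article's Trial status section says recruitment is already under way. The article also says that similar models will serve WHODAS 2.0 and CAGE, so the gap carries over to those outcomes.

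**Working it through.** **Inputs from the article.** 8 provinces × 2 districts × 2 communes = 32 communes in 16 districts. Two orders, two visits (months 1 and 2), and a switch at 4 months. Eight completed participants per commune. Entry requires SRQ-20 above 7. **Assumption:** one commune of each order per district.

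**The plan's own count.** 32 × 8 = 256, as stated. With one case per 14 days, 4 months (about 120 days) gives 120 / 14 ≈ 8.6 cases per commune. So 256 fits one condition-period per commune, as the Power calculation section words it. The Design section instead gives eight per year. Which phases enter the primary contrast is shown in Figure 2, which is not reproduced in the text available, so I carried three readings:

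- A: all communes contribute in both periods.
- B: control-first communes contribute in both periods, SSM-first communes in the first only.
- C: every commune contributes one condition only.

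**Step 1: the listed terms.** Commune as a fixed factor takes 32 columns (intercept included), visit 1 and a varying baseline value 1, which makes 34 columns. Order is the sum of the commune indicators over the communes of that order, so it adds a column and no information.

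| Model | Columns | Rank |
|---|---|---|
| commune + visit + baseline | 34 | 34 |
| the same + order | 35 | 34 |
| the same, without order, baseline read as non-caseness | 34 | 33 |

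These ranks are the same under A, B and C. The third row is a separate problem: everyone is a case at entry, so the baseline value of a non-caseness response is 0 for all and adds nothing.

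**Step 2: what happens if an SSM/control term is added.**

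| Terms, with visit and baseline | A (rank/columns) | B | C |
|---|---|---|---|
| fixed commune + treatment | 35/35 | 35/35 | 34/35 |
| fixed commune + treatment + period | 36/36 | 35/36 | not applicable |
| district + treatment | 19/19 | 19/19 | 19/19 |
| district + treatment + period | 20/20 | 20/20 | not applicable |

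Under C, treatment equals order and stays aliased with commune. Under B, treatment minus period equals the order indicator, so the two cannot be separated while commune is fixed. Only A survives with fixed communes. With district in place of fixed commune, treatment is estimable under all three.

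**Step 3: leaving period out, conditional on both phases being used.** Simulation under A, with 1000 trials per setting, no true effect, 8 participants per commune-period, a 50% control non-case rate and a latent-scale ICC of 0.05. The control rate, the latent scale and the period effects are my assumptions. Reading A with 8 per commune-period needs 32 × 8 × 2 = 512 participants, twice the stated total.

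| Assumed period log-odds ratio | Median estimate, no period term | Type I error, no period term | Type I error, with period term |
|---|---|---|---|
| 0 | 0.00 | 4.4% | 6.5% |
| 0.3 | 0.33 | 23.3% | 6.1% |
| 0.6 | 0.62 | 62.8% | 5.0% |

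Without a period term, the model reports the time trend as if it were the SSM effect.

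**The case against.** The strongest reply is that the article calls its analysis section an overview and leaves detail to the SAP. That covers link details, block sizes and sensitivity analyses. It does not cover this, because the article already fixes the response, distribution, software and terms, and says the proportions model prevails as the prespecified one. The defect is in what is stated.

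A second reply is that order may simply mean treatment. The 32 × 8 = 256 count fits one condition per commune, and on that reading order is the treatment indicator for the primary contrast. This stands as a possibility, so the argument about secular trend has to remain conditional. It does not rescue the model, because order is still absorbed by the commune effects.

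Three stronger readings are tempting, and the article does not support them:

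- A reader might infer that leaving out the district stratum is a fault of this model. With fixed communes it is not: adding 16 district columns leaves the rank at 34. District matters only once commune is no longer fixed.
- A reader might infer that the "3-month intervals over the study" fail to model time because they straddle the 4-month switch. They are a way of laying out descriptive statistics and say nothing about the primary model.
- A reader might infer that the design cannot identify the effect, or that the result is biased by a particular amount. The failure lies in the term list, not the design, and the article gives no figure for drift over time.

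**Conclusion.** The point holds in this form. The listed primary model contains no SSM/control term, and order is exactly aliased with the fixed commune effects (35 columns, rank 34). It therefore cannot return the primary contrast under any of the three readings of which data enter. This rests only on order being constant within a commune and on glm having no random effects, both of which follow from the text. A further rank is lost if baseline is taken literally as non-caseness.

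The calendar-period problem is conditional on control-first communes contributing both phases to the primary contrast. The stepped-wedge wording suggests that they do, while the 256 total leaves it open. If they do, omitting period raised the type I error to about 23% and 63% for assumed period log-odds ratios of 0.3 and 0.6. Those figures illustrate the risk and do not predict this trial's result. The sample size calculation is not affected by this point. The correction should be made before the data are analysed.

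**What to change.** Restate the primary model in the protocol and carry it into the SAP:

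- Make the commune's SSM/control status at the participant's enrolment the effect of interest.
- Drop order and the fixed commune effects. Use a mixed logistic model with a random commune intercept, or GEE with a small-sample correction for 32 clusters.
- State which phases enter the primary contrast. If both do, add a calendar-period term cut at the 4-month switch.
- Include district, the randomisation stratum, now that commune is no longer fixed.
- Adjust for baseline SRQ-20 score in place of baseline caseness.
- The visit term may stay, with the month-2 contrast reported.

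Use the same structure for WHODAS 2.0 and CAGE.

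The cost is wording, with no new data. The statistical price is in degrees of freedom: 16 district strata take 15 of the 31 between commune (32 − 1), leaving 16 before treatment is fitted. A random district effect is an acceptable alternative if that is thought too dear.

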The SSM approach is fitting for community-based settings in LMICs, as it requires minimal resources, can be implement by primary care or lay providers using a task-shifting approach, and can be adapted to meet local settings. A SSM approach is consistent with the call by the global health community for “frugal innovations” that use few resources to meet pressing challenges [20, 21]. Evidence about the effectiveness of SSM in LMIC settings, however, is needed.

From 2013 to 2015, we conducted a pilot study in Hanoi, Vietnam to test the feasibility of training primary care providers to screen for, and treat, mild-to-moderate depression using SSM. The pilot study also tested the feasibility of conducting a full-scale randomized controlled trial (RCT), including the feasibility of primary care provider and patient recruitment. The pilot study demonstrated proof of concept and the SSM intervention was found to be acceptable and effective for use in Vietnam. At baseline, patient (*n* = 71) scores on the Self-reporting Questionnaire-20 (SRQ-20), a measure of depression symptoms that has been validated in the Vietnamese context [22, 23], varied from 8 to 17 (out of a possible 20) with a mean score of 10.9. Administrative errors led to a failure to obtain routine follow-up of SRQ-20 scores at the planned 2-month time period, but follow-up scores were eventually obtained for all participants (time between scores varied from 62 to 241 days). Upon follow-up, SRQ-20 scores varied from 1 to 13 with a mean score of 4.7, with 62/71 (87%) patients having SRQ-20 scores in the normal range.

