### Informed consent

Written informed consent will be obtained from participants at recruitment, following initial screening using the SRQ-20 and prior to WHODAS 2.0 and CAGE assessment. Informed consent will be obtained by trained health workers, and a copy of the Information Letter and Consent Forms will be provided to participants.

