### Inclusion and exclusion criteria

Inclusion criteria for the study are: (1) participant meeting caseness based on an SRQ-20 score of >7 and (2) consent of participant to participate and complete all measures. Exclusion criteria are: (1) cognitive disturbance, (2) symptoms of severe mental illness, including psychosis, severe depression and suicidal ideation, (3) visual or hearing impairment such that patients cannot use the manual or work with a care provider and (4) illiteracy. Patients presenting with symptoms of severe mental illness, including severe depression, will be referred to specialist services at the time of screening.

If patients enrolled in the study should become suicidal or experience psychotic symptoms during the study, primary care providers and social workers will be instructed to refer patients to tertiary care. Patients receiving treatment in tertiary care will no longer remain in the study. Every effort will be made to follow up and conduct outcome measures with these patients; however, the severity of their illness and nature of their treatment may make this difficult.

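### The baseline covariate in the primary SRQ-20 non-caseness model is zero for everyone by eligibility, so the planned baseline adjustment has no effect

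*Protocol article*

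**What the plan says.** All references are to the protocol article.

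- **Response (Analysis).** The plan states that "the primary analysis will consider the proportions of non-caseness with the SRQ-20 within commune as the response variable", fitted by binomial logistic regression.
- **Covariates (Analysis).** The term at issue is the "baseline value of the response variable". In full: "The independent variables will be the cluster (commune), order of administration, and baseline value of the response variable", followed by the timing of the response at months 1 and 2.
- **Entry (Inclusion and exclusion criteria).** The first inclusion criterion is "participant meeting caseness based on an SRQ-20 score of >7".
- **Primary measure (Design).** It is the proportion of participants who "went from being a case of depression (SRQ-20 > 7) to being non-case (SRQ-20 < 8", so all are cases at the start.
- **When the entry SRQ-20 is taken (Informed consent).** Consent is obtained "following initial screening using the SRQ-20 and prior to WHODAS 2.0 and CAGE assessment". No second SRQ-20 is placed after consent.
- **Raw score (Analysis).** "the raw scores from the SRQ-20 within commune will also be modeled", but as a separate model that gives way to the proportions model if the two differ.
- **Pilot baseline (Background).** Scores "varied from 8 to 17 (out of a possible 20) with a mean score of 10.9".

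**The concern.** A baseline covariate is useful only if it differs between participants. Here the response is being below the cut-off of 8, and everyone is enrolled because they are at or above it. The baseline value of that response is therefore the same for all.

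The starting score itself does vary and should predict the endpoint: a participant entering at 8 becomes a non-case with a 1-point drop, one entering at 17 needs a 10-point drop. Severity could also differ between conditions for reasons other than chance. The Analysis section says randomisation has already been implemented, and Trial status says recruitment is under way. Screening and baseline measurement are done by local staff, whose training differs by condition. The documents show no such imbalance, but the primary model as written could not correct one. A reader of the results would nevertheless believe that a baseline adjustment had been made.

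**Working it through.** **Plan's own figures.** No stated figure is in dispute. The sample size reproduces: a two-sample t-test with d = 0.5, two-sided alpha 0.05 and 80% power needs 63.77, so 64 per arm and 128 in total. The design effect is 1 + (8 - 1) × 0.05 = 1.35, and 128 × 1.35 = 172.8, so 173. This calculation takes no credit for baseline adjustment.

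**Step 1: value of the covariate.** Non-caseness means SRQ-20 < 8 and entry means SRQ-20 > 7. On an integer score no enrolled participant satisfies both at baseline. The count is 0 of the planned 256 (32 communes × 8), and the variance is 0.

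**Step 2: effect on the model.** Layout: 32 communes × 8 participants × 2 visits, each commune contributing one condition. Baseline scores were drawn uniformly from 8 to 17 and the other parameters were assumed.

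| Terms (with intercept) | Columns | Rank |
|---|---|---|
| order, month | 3 | 3 |
| order, month, baseline non-caseness | 4 | 3 |
| order, month, individual baseline score | 4 | 4 |
| commune, order, month | 34 | 33 |
| the same + baseline non-caseness | 35 | 33 |
| the same + commune-mean baseline score | 35 | 33 |
| the same + individual baseline score | 35 | 34 |

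The planned covariate adds no rank. In the model without commune terms, the deviance (685.587), the order coefficient (0.6138) and its standard error (0.1813) are the same with and without it. The individual score does add rank; in these data it lowers the deviance to 593.6, though the size of that drop reflects the assumed slope. A commune-mean score adds nothing once commune terms are present.

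**Step 3: what the lost adjustment is worth.** The documents give no correlation r between baseline and follow-up score, so r = 0.3 to 0.5 is assumed.

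- For a linear model of a continuous score, the variance removed is r² = 0.09 to 0.25, and 1/(1 - r²) = 1.10 to 1.33, that is, 10-33% more participants.
- The primary model is logistic on a dichotomised score. A simulation with a latent normal score, d = 0.5, control non-case rates of 30%, 50% and 70%, no clustering and 400,000 participants per setting gave:

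| Control rate | r | SE of log odds ratio, adjusted / unadjusted | z², adjusted / unadjusted |
|---|---|---|---|
| 30% | 0.3 | 1.03 | 1.05 |
| 30% | 0.5 | 1.10 | 1.16 |
| 50% | 0.3 | 1.03 | 1.06 |
| 50% | 0.5 | 1.10 | 1.16 |
| 70% | 0.3 | 1.03 | 1.05 |
| 70% | 0.5 | 1.09 | 1.16 |

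The standard error rises slightly because the adjusted log odds ratio moves away from zero by more, so the gain is read from z². It is 5-16% here; roughly 4-17% allows for simulation error.

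**The case against.** **The authors may have meant the raw score.** The protocol calls the SRQ-20 the primary outcome measure and says it can be used as a score or as a rate, and the same model description is reused for WHODAS 2.0 and CAGE, where a baseline value makes sense. This is the best defence and may well be the intention. But the sentence before the covariate list defines the response as the non-case proportion, and the raw score is given its own model. If the score was meant, the wording needs the same correction.

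**A second SRQ-20 might serve as baseline.** The Abstract has blinded assessors taking SRQ-20 scores at baseline, and such a reading could fall below 8. The Blinding and Data collection sections contradict this: assessors make only the 1- and 2-month calls, and local staff collect baseline data. The Design section also has every participant start as a case.

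**Detail is deferred to the SAP.** Omitted coding could be left there. This covariate is not omitted: the protocol names it, and it cannot work.

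**The harm is limited.** This stands. A reader might infer that the constant biases the treatment effect; it does not, because software drops it. A reader might also carry over the linear-model figure of 10-33% more participants; that does not apply to a logistic model of a dichotomised score. Nor does the problem extend to the raw SRQ-20, WHODAS 2.0 and CAGE models, whose baseline values are not fixed by the entry rule. The raw-score model offsets the loss only in part, because it yields to the proportions model.

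**Conclusion.** The point holds for the primary SRQ-20 proportions model. As written, its baseline term is a constant and the analysis is unadjusted for baseline severity. That conclusion follows from the response definition and the entry criterion and needs no assumption beyond the screening SRQ-20 being the baseline, which the body of the protocol supports.

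The cost is modest: roughly 4-17% in effective sample size, resting on an assumed correlation of 0.3 to 0.5 and a simulation without clustering, plus no protection against an imbalance in severity that is possible but not shown. Because the sample size calculation did not count on adjustment, the planned number of participants is not undermined on this account. The point is a should-fix.

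**What to change.** In the Analysis section and the SAP, replace the baseline value of the response with each participant's baseline SRQ-20 total score, entered as a continuous covariate. Fit the primary binomial model to individual responses rather than commune proportions, since a commune-mean score would be absorbed by the commune terms. Allow for the correlation between a person's month-1 and month-2 responses. Make the change before the data are analysed, so that the covariate remains prespecified.

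The cost is small but not nil. The score is already collected; the analysis becomes an individual-level repeated binary model, and the odds ratio becomes conditional on baseline score, which the report should say.

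One related matter needs settling at the same time: commune terms and order of administration together are rank deficient (34 columns, rank 33) if each commune contributes a single condition. Changing the covariate does not cure that, so the form in which commune enters the model must also be stated.
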